#### Qualitative trustworthiness

2.6.3

For the embedded qualitative interviews, methodological rigor will be established through the widely accepted framework of trustworthiness, comprising the four interrelated criteria of credibility, dependability, confirmability, and transferability.

Credibility (Internal Validity). To ensure that the analytical findings authentically reflect participants’ lived realities, member checking will be employed. Following transcription, interview transcripts will be returned to the respective participants to verify their accuracy and to confirm that participants’ experiences, perceived benefits, and reported challenges have been faithfully captured. Data triangulation will be further achieved by eliciting and contrasting perspectives from both the patients receiving the intervention and the medical staff delivering it, thereby strengthening the validity of the emergent themes.

Dependability (Reliability). To minimize individual interpretive bias and establish a robust coding framework, data analysis will be conducted independently by no fewer than two qualitative researchers. Each researcher will code the transcripts separately, and any discrepancies in thematic generation will be reconciled through consensus meetings. NVivo software will be used to support this process by maintaining a transparent and traceable audit trail throughout the coding procedure.

Confirmability (Objectivity). It is acknowledged that the researchers’ prior clinical experience and professional background may inadvertently shape both the interview process and subsequent data interpretation. To mitigate this risk, researchers will engage in active reflexivity by maintaining reflective journals throughout the data collection and analysis phases, enabling them to identify and bracket personal assumptions in order to preserve interpretive objectivity.

Transferability (External Validity). To allow future researchers and clinicians to evaluate the applicability of the qualitative findings to other contexts, rich and thick descriptions will be provided. By comprehensively detailing the clinical setting, the demographic characteristics of participants with MCI, and the specific nature of the combined rTMS and DMI interactions, readers will be sufficiently equipped to assess the relevance of this multimodal intervention to broader geriatric populations.

### Sample size

2.7

A priori power analysis (G*Power 3.1) was conducted for a four-group repeated measures ANOVA (interaction effect). To detect a medium effect size (f = 0.25) with a power of 0.8 and an alpha level of 0.05, a total sample of approximately 128 participants (32 per group) is required. To account for potential participant dropouts, we have factored in an anticipated attrition rate of 20% over the 24-week study period (12-week intervention plus 12-week follow-up). This 20% estimate is intentionally conservative and rigorously justified by previous longitudinal literature involving older adults with cognitive impairment. Systematic reviews of intensive, multi-modal non-pharmacological interventions (including aerobic exercise and neuromodulation protocols) in geriatric populations consistently report attrition rates ranging from 15% to 21%, typically due to transportation barriers, intervention fatigue, or unrelated emergent health issues (Di Lorito et al., 2020). Therefore, to ensure the trial remains adequately powered throughout the follow-up phase, we aim to recruit a final total of 160 participants (40 per group).

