### Trial design

2.1

This study will adopt a four-arm, single-blinded, parallel-group randomized controlled trial (RCT) design, chosen to comprehensively evaluate the individual and synergistic effects of repetitive transcranial magnetic stimulation (rTMS) and a dance movement intervention (DMI). Participants will be randomly assigned in a 1:1:1:1 ratio to one of four parallel groups: (1) a Combined Intervention Group, receiving active rTMS followed by the DMI (Chinese Square Dance); (2) an rTMS Only Group, receiving active rTMS and a time-matched, non-aerobic social activity control; (3) a DMI Only Group, receiving sham rTMS followed by the DMI; and (4) a Control Group, receiving sham rTMS and the social activity control. The research protocol will adhere to the Standard Protocol Items: Recommendations for Interventional Trials (SPIRIT) guidelines (Chan et al., 2013) and the Consolidated Standards of Reporting Trials (CONSORT) statement for non-pharmacologic treatments (Barbour et al., 2017), and the study will be conducted in accordance with the Declaration of Helsinki (Association, 2025) and has been registered at Chinese Clinical Trial Registry (ChiCTR2600127655). All procedures will be carried out at the Department of Rehabilitation, Handan Central Hospital, Handan, China (see **Figure 2**).

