##### Factorial analysis for synergistic effects

2.9.1.3

To directly address the study’s aim of elucidating synergistic mechanisms and to capitalize on the robust factorial design, a 2 × 2 factorial analysis will be nested within the models. The main effect of the rTMS factor (active vs. sham), the main effect of the DMI factor (active vs. sham), and the rTMS × DMI interaction effect on the primary outcome will be tested. A statistically significant positive interaction term will quantitatively support the hypothesis that the combined intervention produces benefits exceeding the additive effects of the individual modalities.

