## Conclusions

4

We hypothesize that the combined rTMS and DMI group will demonstrate superior and more durable improvements in global cognition and physical performance compared to the monotherapy or control groups. By providing a comprehensive, mixed-methods evaluation of this synergistic approach, this trial aims to inform future clinical guidelines and offer a feasible, culturally appropriate strategy for managing MCI in the aging population.

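### The sample size of 128 is not reproduced by the repeated-measures interaction test it is attributed to, and the power for the rTMS x DMI synergy test is not stated

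*Protocol article*

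**What the plan says.** Section 2.7 of the protocol article gives the calculation in a few lines. The test: "A priori power analysis (G*Power 3.1) was conducted for a four-group repeated measures ANOVA (interaction effect"). The inputs: "a medium effect size (f = 0.25) with a power of 0.8 and an alpha level of 0.05". The result: "a total sample of approximately 128 participants (32 per group) is required". Allowing for "an anticipated attrition rate of 20% over the 24-week study period", the target becomes 160: "we aim to recruit a final total of 160 participants (40 per group"). Section 2.7 does not give the number of measurements, the correlation between them, epsilon, the numerator degrees of freedom or the effect-size convention.

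Two different interactions appear in the analysis sections. Section 2.9.1.2 makes Group x Time over T0, T1 and T2 the main indicator of efficacy. Section 2.9.1.3 tests rTMS x DMI on the primary outcome and says: "A statistically significant positive interaction term will quantitatively support the hypothesis that the combined intervention produces benefits exceeding the additive effects". Section 2.7 does not say which of the two it means. Sections 2.4.1 and 2.10 define the primary outcome as the T0 to T1 change in MoCA, and section 2.9.1.4 adjusts for baseline MoCA, age, gender and education.

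**The concern.** A sample size paragraph should let a reader put its inputs into the named test and recover the number. Here the named test needs either far fewer participants or a clearly different number, depending on settings that are not given. The stated 80% power is therefore tied to no identifiable hypothesis.

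The trial's title and its factorial section are about synergy. A reader who sees the words interaction effect and medium effect size beside 80% power may think the synergy test is covered at an ordinary effect size. On the one-degree-of-freedom test that yields 128, the detectable synergy is twice the detectable main effect, and nothing in section 2.7 shows this.

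**Working it through.** **Inputs.** From the protocol article: four equal groups (2.1), f = 0.25, alpha 0.05, power 0.80, N = 128, attrition 20% (all 2.7). Time points: three in the mixed model (2.9.1.2), two for the primary change (2.10). Assumed, because not given: correlation rho, epsilon, effect metric. Power is from the noncentral F distribution, with N searched in steps of 4.

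**Dropout step.** 128 / (1 − 0.20) = 160. This reproduces.

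**Named test: Group x Time, k = 4 groups, m visits.** Degrees of freedom are 3(m − 1) and (N − 4)(m − 1) at epsilon 1. The noncentrality is:

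- default metric: λ = f² N m / (1 − rho)
- SPSS metric: λ = f² (N − 4)(m − 1)
- Cohen metric: λ = f² N (m − 1)

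| Setting (epsilon 1) | m = 2: N needed | m = 3: N needed |
|---|---|---|
| Default, rho 0 | 92 | 76 |
| Default, rho 0.5 | 48 | 40 |
| Default, rho 0.9 | 16 | 12 |
| SPSS metric | 184 | 120 |
| Cohen metric | 180 | 116 |

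Example: default, m = 3, rho 0.5, N = 40 gives λ = 0.0625 × 40 × 3 / 0.5 = 15.0 and power 0.805. At N = 128 and rho 0.5, the default calculation has power above 99.8%. No entry is 128.

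**A test that gives 128.** A fixed-effects ANOVA with four cells and 1 numerator df has λ = f² N = 0.0625 × 128 = 8.0 on 1 and 124 df, and power 0.801. At N = 124, power is 0.789. So 128 is the exact answer for a between-subject 2x2 main effect or interaction.

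**Other routes to 128.** With three visits, the SPSS metric at epsilon 0.90 (power 0.815) or the Cohen metric at epsilon 0.85 (0.812). Also the repeated-measures between-group test, which is not an interaction, at rho 0.4 with two visits or 0.55 with three (0.807). None of these settings is stated.

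**What f = 0.25 means in the 1-df test.** Let σ be the SD of the analysed variable.

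- Main effect δ: marginal means lie ±δ/2 from the grand mean, so f = δ / (2σ) and δ = 0.5σ.
- rTMS x DMI: let Δ be the combined-arm gain beyond the sum of the two separate effects. The interaction component in each cell is ±Δ/4, so f = Δ / (4σ) and Δ = 1.0σ.

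**Power for synergy, no covariate gain,** λ = (Δ/4σ)² N:

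| Δ / σ | 128 analysed | 160 analysed |
|---|---|---|
| 0.25 | 11% | 12% |
| 0.50 | 29% | 35% |
| 0.75 | 56% | 65% |
| 1.00 | 80% | 88% |

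The smallest Δ with 80% power is 1.00σ at 128 and 0.89σ at 160.

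**Counting baseline adjustment.** If baseline and T1 MoCA correlate at r (assumed), the residual SD is √(1 − r²) times the raw SD, so λ is divided by 1 − r². For Δ = 0.5 raw SD and N = 128, unadjusted λ = 0.125² × 128 = 2.0:

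- r = 0.5: λ = 2.0 / 0.75 = 2.67, power 37%
- r = 0.7: λ = 2.0 / 0.51 = 3.92, power 50%
- r = 0.8: λ = 2.0 / 0.36 = 5.56, power 65%

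The synergy with 80% power, in raw SD, is then about 0.87, 0.71 and 0.60.

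**The case against.** The strongest reply has four parts.

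First, the exact match with the 2x2 test is only a numerical match. A reader might infer that the sponsor ran that test and mislabelled it. The article does not say so, it gives the figure as approximate, and the repeated-measures settings listed above also reach 128. This stands: the origin of 128 is unknown.

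Second, a reader might infer that the protocol claims 80% power for synergy and that the claim is false. The document does not support that either. In a four-group repeated-measures ANOVA, interaction most naturally means Group x Time. The introduction places synergistic mechanisms among the secondary aims. The Conclusions state a hypothesis, that the combined group "will demonstrate superior and more durable improvements in global cognition and physical performance compared to the monotherapy or control groups", and attach no power to it. This also stands: the synergy power is unstated rather than misstated.

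Third, if the default Group x Time calculation was intended, 128 is more than it needs, so the fault is a wrong attribution rather than a shortage for that test. This stands under the default metric. It does not hold for the SPSS or Cohen metric with two visits, where 180 to 184 would be needed.

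Fourth, the planned baseline adjustment raises power above the unadjusted figures. It does, but even at an assumed correlation of 0.8 a 0.5 SD synergy stays at about 65% with 128 analysed.

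None of this recovers 128 from the test as section 2.7 describes it. Nor is the problem merely detail left to an analysis plan: the paragraph names a test and gives a number that does not follow from it without unstated, non-default settings.

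**Conclusion.** The point holds in limited form. The figure of 128 is not reproduced by the named test at the stated f, alpha and power: not under the default metric at any correlation from 0 to 0.9, nor under either alternative metric at epsilon 1. It coincides exactly with a 1-df between-subject 2x2 test, which is a plausible origin but not an established one. The word interaction is ambiguous between Group x Time and rTMS x DMI.

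Whatever its origin, 128 analysed gives 80% power for a main effect of 0.5 SD and for an rTMS x DMI excess of about 1.0 SD, both in SD of the analysed variable. For a 0.5 SD synergy, power is about 29% unadjusted, about 37% to 65% in raw MoCA SD units with baseline adjustment (r assumed 0.5 to 0.8), and 35% if all 160 are analysed without adjustment. The article gives no MoCA SD, so these cannot be turned into points without a further assumption.

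The design is not invalidated: main effects of 0.5 SD are adequately powered, and the attrition step is correct. Nor does the article say that a non-significant interaction would mean no synergy; the low power is a reason to rule that reading out in advance.

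**What to change.** - Correct section 2.7 to the test actually run, with its numerator df, number of measurements, correlation, epsilon and effect metric. If those settings cannot be recovered, recompute for the planned primary contrast on the T0 to T1 MoCA change. The 2x2 test should not be written in as the source merely because it yields 128.
- Say whether interaction in 2.7 means Group x Time or rTMS x DMI.
- State separately that 128 analysed gives 80% power for a 0.5 SD main effect and for an rTMS x DMI interaction of only about 1.0 SD of the analysed variable. Give the power for smaller synergies, with any assumed baseline correlation shown.
- Add to 2.9.1.3 that the interaction estimate will be reported with its confidence interval and that a non-significant result will not be read as absence of synergy.

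Recruitment stays at 160, with no change to design or conduct. The cost is one rewritten paragraph, one added sentence and a less favourable stated power for synergy.

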### Randomization-sequence generation and blinding

2.8

Participants will be randomly allocated to one of the four groups using a computer-generated randomization sequence. Allocation concealment will be ensured using sealed, opaque envelopes, which will be opened by a researcher not involved in assessment or intervention delivery. This is a single-blinded trial. Outcome assessors will be blinded to the group allocation of participants. Due to the nature of the interventions, participants and instructors cannot be blinded. However, participants will be instructed not to discuss their intervention with the assessors.

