#### rTMS intervention (active and sham)

2.3.1

Participants in the Combined Intervention and rTMS Only groups will receive active rTMS. Sessions will be conducted 5 days per week for the first 4 weeks (induction phase), followed by 2 sessions per week for the remaining 8 weeks (maintenance phase). Each session will involve intermittent theta burst stimulation (iTBS) over the left dorsolateral prefrontal cortex (DLPFC). The iTBS protocol consists of bursts of 3 pulses at 50 Hz, repeated at 5 Hz. A total of 600 pulses will be delivered per session (2 seconds on, 8 seconds off, for 190 seconds) at 70–80% of the individual’s resting motor threshold (rMT). A 7-cm figure-of-eight coil connected to a magnetic simulator will be used, with neuronavigation to ensure consistent targeting.

For participants in the Combined Intervention group, the sequence and timing of the two modalities are strictly controlled to maximize the neuroplastic priming effect. The iTBS will always be administered prior to the DMI. Following the completion of the 3-minute iTBS session, participants will commence the DMI within a strict 10- to 15-minute window. This specific timing interval is chosen based on neurophysiological evidence demonstrating that a single block of iTBS induces a transient state of enhanced cortical excitability and long-term potentiation (LTP)-like plasticity that peaks shortly after stimulation and lasts for approximately 20 to 30 minutes (Huang et al., 2005; Tse et al., 2018). Initiating the cognitively and physically demanding dance routines within this critical time window ensures that the activity-dependent neuroplasticity driven by the DMI coincides with the iTBS-induced state of heightened cortical receptivity, thereby optimizing the synergistic therapeutic effects (Stoykov and Madhavan, 2015).

Participants in the DMI Only and Control groups will undergo a sham rTMS procedure. A placebo coil that produces an equivalent sound and scalp sensation without inducing a therapeutic magnetic field will be used to maintain blinding.

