#### Blinding integrity assessment

2.6.2

To rigorously evaluate the success of the single-blind design and ensure that treatment effects are not confounded by participant expectations, a formal assessment of blinding integrity will be conducted. At the conclusion of the 12-week intervention phase (T1), all participants will be asked to complete a standardized blinding questionnaire. Participants will be asked to guess their assigned intervention arm (e.g., “Active iTBS + Dance,” “Sham iTBS + Dance,” etc.) and to state the primary reason for their guess (e.g., perceived physical sensations, perceived cognitive improvement, or random guess) (Kolahi et al., 2009).

The blinding efficacy will be quantitatively evaluated using Bang’s Blinding Index (BBI), a validated statistical metric that ranges from -1 (complete opposite guessing) to 1 (complete unblinding), with 0 indicating perfect blinding (random guessing) (Bang et al., 2004). The BBI will be calculated separately for the active and sham iTBS conditions to determine if the sham coil successfully mimicked the somatic sensations of active stimulation without unmasking the participants (Berlim et al., 2013). If the BBI indicates significant unblinding, the participant’s guess will be included as a covariate in the secondary sensitivity analyses to adjust for potential expectancy biases.

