#### Dissemination

3.7.6

The findings of this trial will be disseminated through multiple channels to maximize their scientific and clinical impact. The primary results, encompassing both the quantitative efficacy outcomes and the qualitative findings from the embedded interview component, will be submitted for publication in a peer-reviewed, open-access journal. Interim and final results will also be presented at relevant national and international academic conferences in the fields of neurology, cognitive rehabilitation, and geriatric medicine.

In accordance with international clinical trial transparency guidelines, the trial registry record (ChiCTR2600127655) will be updated with summary results within 12 months of study completion. A lay summary of the findings will be provided to all participants upon request. Authorship of all publications arising from this study will adhere to the criteria established by the International Committee of Medical Journal Editors (ICMJE). No professional medical writers will be employed without full disclosure in the acknowledgements section.

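### Section 2.8 says participants cannot be blinded, contradicting the sham coil and the participant blinding check; the rule to adjust for the Week 12 guess biases that sensitivity estimate

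*Protocol article*

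**What the plan says.** All references are to the protocol article.

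- **Section 2.8** calls the trial single-blinded and names the blinded party: "Outcome assessors will be blinded to the group allocation of participants". It then says: "Due to the nature of the interventions, participants and instructors cannot be blinded". No distinction is made between the rTMS factor and the dance factor.
- **Section 2.3.1**, for the DMI Only and Control groups: "A placebo coil that produces an equivalent sound and scalp sensation without inducing a therapeutic magnetic field will be used to maintain blinding".
- **Section 2.6.2** sets out a blinding check. Its aim: "To rigorously evaluate the success of the single-blind design and ensure that treatment effects are not confounded by participant expectations". At T1, "all participants will be asked to complete a standardized blinding questionnaire", guessing their arm and giving the main reason; perceived cognitive improvement is one example of a reason. Bang's index is computed separately for the active and sham iTBS conditions. If it shows significant unblinding, the participant's "guess will be included as a covariate in the secondary sensitivity analyses to adjust for potential expectancy biases".
- **Section 2.9.1.3** tests the rTMS main effect (active versus sham), the DMI main effect and their interaction on the primary outcome.
- **Section 2.10** fixes the primary outcome as MoCA change from T0 to T1, so the guess and the primary outcome belong to the same assessment point.

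**The concern.** There are two linked problems.

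First, the statement in 2.8 cannot stand beside 2.3.1 and 2.6.2. Assessors do not need a sham coil in order to be blinded, so the placebo coil can only serve to mask participants. If participants could not be masked to the coil, the sham would not control expectancy, and a participant blinding index would have nothing to test. MoCA depends on the participant's own performance, so blinded assessors limit detection bias but not expectancy. The rTMS and interaction contrasts need participant masking to be stated correctly.

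Second, the guess is collected after 12 weeks of treatment. Someone who has improved may guess active because of the improvement. Adjusting for that guess conditions on a consequence of treatment and outcome, which distorts the rTMS estimate it is meant to protect.

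**Working it through.** **Step 1. Blinding by factor, as the text implies it.**

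| Question | 2.8 | 2.3.1 | 2.6.2 |
|---|---|---|---|
| Are participants masked to active/sham iTBS? | No (blanket statement) | Yes (purpose of the placebo coil) | Presumed yes, and tested |
| Are participants masked to dance/social? | No | not addressed | not addressed |
| Who is the single-blind party? | Assessors | not stated | Participants are the ones questioned |

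The first row is a contradiction. The second is unavoidable and harmless to the rTMS contrast. No other section reconciles the first row.

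**Step 2. Inputs for the covariate check.** The plan gives no figure for this point, so there is none to reproduce. From section 2.7: 160 randomised with 20% attrition gives 160 × 0.8 = 128, or 32 per arm. Each rTMS level pools two arms: 2 × 32 = 64. The guess model and its slopes are assumptions; the documents give none.

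**Step 3. Model.** Let T = 1 for active and 0 for sham, Y the change in SD units, and G = 1 for a guess of active.

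- Outcome: Y = δT + e, with e ~ N(0, 1)
- Guess: logit P(G = 1) = s(2T − 1) + β(Y − δ/2), where s is sensory leakage and β is guessing driven by own change
- Unadjusted estimate: coefficient of T in Y on T. Adjusted estimate: coefficient of T in Y on T and G
- Bang's index with no don't-know answers: 2 × (proportion guessing correctly) − 1, with SE = √((1 − index²)/n)

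**Step 4. Perfect sham (s = 0), true effect δ = 0.50 SD.**

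| β per SD | Adjusted effect (SD) | Change | Bang's index, each condition |
|---|---|---|---|
| 0.5 | 0.48 | −4% | 0.06 |
| 1.0 | 0.42 | −16% | 0.10 |
| 1.5 | 0.36 | −28% | 0.13 |
| 2.0 | 0.32 | −36% | 0.15 |

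The unadjusted estimate stays at 0.50. A rerun agrees within about 0.01. The index rises above zero although the coil gives nothing away.

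**Step 5. How often the trigger is met in Step 4.** At β = 1.5 the SE is √((1 − 0.13²)/64) ≈ 0.12, so an index of 0.13 is about one SE from zero. Reading significant unblinding as a 95% interval above zero in at least one condition, the trigger is met in about 15% of runs at β = 0.5 and about 37% at β = 1.5. The rerun gave about 43% at β = 2.0.

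**Step 6. True null (δ = 0) with sensory leakage (s = 1) and change-driven guessing.** The adjusted estimate is about −0.2 SD at β = 0.5 and −0.33 SD at β = 1.0, against 0.00 unadjusted. The trigger is met in over 99% of runs.

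**Step 7. On the MoCA scale** (80 per level, assumed SD of change 2.5). A true 2-point effect with a perfect sham is adjusted to 1.66 at β = 0.4 per point and 1.27 at 0.8. With s = 1 and β = 0.4, a true null becomes −0.83 points and is rejected in 54% of runs, against about 5% unadjusted.

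**Step 8. What participant masking protects.** Take a true null in which believing oneself on active adds 1 point and guesses follow sensory cues alone (index about 0.46 to 0.76). The unadjusted effect is 0.46 to 0.76 points, with rejection in 21% to 48% of runs.

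**The case against.** **The contradiction is only loose wording.** Nothing tells staff to disclose the coil, the arms are labelled sham throughout, and 2.8 most plausibly had dance versus social activity in mind. This stands as far as intent goes. A reader might infer that participants will in fact be told, or that the sham arms fail to control expectancy; the documents do not support that. The sentence is still wrong as written, and it sits in the section that defines blinding.

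**The guess adjustment touches no main result.** Correct. It is conditional and confined to secondary sensitivity analyses. A reader might infer that the primary rTMS estimate is biased by it; it is not, because the guess is not among the covariates in 2.9.1.4. With a perfect sham the trigger is also missed in most runs, so a single headline such as −28% would rest on one assumed slope and on ignoring the trigger.

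**The adjustment sometimes works.** In the Step 8 setting, where guesses follow sensation only, adjusting returns the estimate to zero. But the plan cannot know it is in that setting, and its own questionnaire lists perceived improvement as a reason for guessing.

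**The questionnaire is sound.** Largely accepted. Asking for the full arm does no harm, since the index is computed for active versus sham. Recording the reason helps to separate benefit-driven from sensation-driven guesses. An assessor guess or an earlier participant guess would be optional additions.

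**Interim presentations.** Section 3.7.6 mentions them, and a reader might infer a breach of assessor blinding. Aggregate results do not reveal an individual's allocation, so that does not follow; it is a separate matter.

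**Conclusion.** The point holds in two parts. The contradiction between 2.8 on one side and 2.3.1 and 2.6.2 on the other is plain from the text and needs no assumption. It matters because the rTMS main effect and the interaction in 2.9.1.3 rest on participants being masked to active versus sham iTBS.

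The guess-as-covariate rule yields a biased secondary sensitivity estimate whenever perceived benefit influences the guess. In the scenarios examined, a true 0.50 SD effect shrinks to between 0.48 and 0.32 SD with a perfect sham. A true null becomes about −0.2 to −0.3 SD when sensory cues leak too, which is the situation in which the rule would almost always be invoked. The downward direction is common to those scenarios; the size depends on guess slopes, a leakage strength and, on the MoCA scale, an SD that the documents do not give. The primary analysis is unaffected.

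**What to change.** 1. **Section 2.8:** replace the blanket statement with blinding by factor. Participants, dance instructors, social-group leaders and outcome assessors are masked to active versus sham iTBS. Dance or social allocation is open to participants and session leaders but masked from assessors.
2. **Section 2.6.2:** delete the rule that adds the guess as a covariate. Report Bang's index for the active and sham conditions, together with the stated reasons for guesses, descriptively beside the rTMS result. Describe the check as testing participant masking to iTBS, rather than the assessor blinding that 2.8 calls single-blind.

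The cost is a few sentences and the loss of one secondary sensitivity analysis. An additional guess early in treatment, before benefit is likely, would be less affected by efficacy but is optional.
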